## Abstract

**Background:**

Pre-eclampsia is a multisystem disorder affecting 2.8% of pregnancies in the UK. It usually presents after 20-week gestation with new-onset high blood pressure and proteinuria. Complications include eclampsia, stroke, and HELLP syndrome for the mother and preterm birth, fetal growth restriction, and stillbirth for the baby. Delivery is the only definitive cure, with antenatal care focusing on early detection and management of complications and optimising timing of delivery. Previous studies have shown calcium supplementation may reduce the risk of pre-eclampsia, but findings are driven by large effects seen in small trials that have not been replicated in larger trials. Subgroup analysis suggests benefits may only be seen in women with low dietary calcium intake, so findings may not be applicable to populations with adequate dietary calcium. Although the largest benefits appear to be in high-risk women, data are very limited, with no large trials conducted.

**Methods:**

CaPE is a two-arm parallel triple-blinded, placebo-controlled, multicentre, superiority randomised controlled trial testing the hypothesis that in pregnant women at increased risk, calcium supplementation is effective in reducing the occurrence of pre-eclampsia. The study will recruit 7756 women from approximately 60 obstetric units in hospitals across the UK. Women with a confirmed viable pregnancy, with gestation 22 + 0 weeks or less and deemed eligible for aspirin therapy based on either NICE guideline criteria (at least one high-risk factor or two or more moderate risk factors) or the Fetal Medicine Foundation (FMF) algorithm will be eligible to be randomised in a 1:1 ratio to receive either 2 g per day of calcium supplementation or placebo taken from 12 to 22 weeks, up to birth. The primary outcome is clinician diagnosis of pre-eclampsia, based on the ISSHP definition. Key secondary outcomes are severe pre-eclampsia index and preterm birth < 37 weeks; other secondary outcomes include the Pre-eclampsia Core Outcome Set (COS).

**Discussion:**

Calcium supplementation in high-risk women is an attractive intervention due to its potential efficacy, low cost, and safety profile, but a definitive trial is required to confirm benefits.

**Trial registration:**

ISRCTN 12033893. Registered on 25 May 2021.

## Administrative information

Note: The numbers in curly brackets in this protocol refer to SPIRIT checklist item numbers. The order of the items has been modified to group similar items (see http://www.equator-network.org/reporting-guidelines/spirit-2013-statement-defining-standard-protocol-items-for-clinical-trials/).

## Introduction

### Background and rationale {6a}

Pre-eclampsia is a multisystem disorder affecting 2.8% of pregnancies in the United Kingdom (UK) [1]. It usually presents after 20 weeks of gestation with new-onset high blood pressure, proteinuria, and/or involvement of other maternal organs [2]. Severe complications include eclampsia, stroke, haemolysis elevated liver enzymes low platelets (HELLP) syndrome, and disseminated intravascular coagulation (DIC). Risks to the fetus are also increased and may present as fetal growth restriction and stillbirth [3]. Pre-eclampsia is a leading cause of iatrogenic prematurity [4]. It also leads to significant National Health Service (NHS) resource utilisation due to increased surveillance, hospital admissions, and higher-level care [5].

The exact cause of pre-eclampsia remains unclear but is thought to occur secondary to poor placentation and endothelial cell damage, leading to vasoconstriction, abnormal coagulation, and organ dysfunction [6]. Once diagnosed, delivery is the only definitive cure, with antenatal care focusing on early detection and management of complications, as well as optimizing timing of delivery. Preventative strategies, including antiplatelet agents (low-dose aspirin) and calcium, may be effective in reducing the risk of pre-eclampsia [5].

A Cochrane review of 77 trials (40,249 women and their babies) demonstrated that aspirin reduces pre-eclampsia risk by 18% [7], with modest benefits in reducing the risk of death in the baby, preterm birth, small for gestational age babies, and having a pregnancy with a serious adverse outcome in women with risk factors for pre-eclampsia. Aspirin may have greater benefits in reducing pre-eclampsia leading to birth prior to 37-week gestation [8]. However, aspirin may slightly increase the risk of bleeding complications including postpartum haemorrhage [9]. National Institute for Health and Care Excellence (NICE) and other international guidelines recommend low-dose aspirin (75–150 mg) from 12-week gestation for women with any high-risk factor or multiple moderate-risk factors for pre-eclampsia, and aspirin is now standard of care in the UK and other parts of the world [10].

Epidemiological studies suggest an inverse relationship between calcium intake and pre-eclampsia risk [11–14]. Calcium may lower blood pressure by reducing parathyroid hormone release and intracellular calcium, which leads to reduced vascular smooth muscle contractility and vasoconstriction and lower resistance in uterine and umbilical arteries, increasing placental perfusion and oxygenation to the baby [15, 16]. A Cochrane review of 14 trials (15,730 women) found calcium supplementation (1.5–2 g daily) reduced pre-eclampsia risk by 55% (*RR* 0.45, 95% *CI* 0.31–0.65), preterm birth by 24% (*RR* 0.76, 95% *CI* 0.60–0.97), and serious maternal morbidity and mortality by 20% (*RR* 0.80, 95% *CI* 0.65–0.97) [17]. Concerns about potential adverse effects, including renal calculi, have not been substantiated in clinical trials [17]. However, the benefits of calcium supplementation for pre-eclampsia may be limited to populations with low dietary calcium intake. Subgroup analysis showed marked risk reduction in women with low baseline dietary calcium intake (*RR* 0.36, 95% *CI* 0.20–0.65; 8 trials, 10,678 women) but not in those with adequate intake (*RR* 0.62, 95% *CI* 0.32–1.20; 4 trials, 5022 women). Trials recruiting high-risk women suggest a 78% reduction in pre-eclampsia risk (*RR* 0.22, 95% *CI* 0.12–0.42; 5 trials, 587 women), though studies are small, use varied definitions of high risk, and recruited women with both adequate and inadequate dietary calcium intake [17]. Large trials in high-risk populations are lacking.

Calcium supplementation for pre-eclampsia prevention is not currently recommended in the UK [10], as prior trials predominantly recruited low-risk women with low dietary calcium intake, so findings have not been viewed as applicable to the UK population. There is limited data on dietary calcium intake in pregnant women in the UK, but three small studies (total 215 women) suggest a mean intake from 720 to 1345 mg/day [18]. However, as calcium supplementation appears to be most beneficial for women at high risk of pre-eclampsia, an adequately powered, large randomised trial is needed to evaluate its efficacy in high-risk women, regardless of baseline dietary calcium intake. The importance of this research question has been recognised by NICE [10]. Calcium is an attractive intervention due to its low cost, safety, and potential for reducing maternal and perinatal morbidity. This research could lead to improved maternal and perinatal outcomes and NHS cost savings.

Combining calcium with aspirin may also have synergy through addressing both vascular dysfunction and coagulation abnormalities, the two primary pathological mechanisms seen in pre-eclampsia. A prior small trial assessing combined therapy was underpowered to detect meaningful differences, highlighting the need for further research [19].

### Objectives {7}

The primary objective is to test the hypothesis that in pregnant women at increased risk of pre-eclampsia, calcium supplementation given in a dose of 2 g per day during pregnancy plus usual care (including aspirin) is more effective than usual care alone in reducing the relative risk for the occurrence of pre-eclampsia by at least 20%.

The secondary objectives are as follows:To assess the impact of calcium supplements on other important outcomes for the woman and babyTo assess the cost-effectiveness of calcium plus usual care compared to usual care aloneTo assess whether calcium has a differential effect in pre-specified subgroups of womenTo assess the degree to which pregnant women are able to adhere to a calcium supplementation regimen

## Methods: participants, interventions, and outcomes

### Trial design {8}

The CaPE trial is a parallel-group, triple-blinded, placebo-controlled, multicentre, two-arm superiority randomised controlled trial with a 12-month internal pilot and health economics evaluation. Participants will be randomised at the level of the individual in a 1:1 ratio to either the equivalent of 2 g per day of calcium supplementation or placebo starting from between 12^+0^ and 22^+0^ weeks gestation and continuing up to delivery. The primary outcome will assess the superiority of calcium supplementation at reducing the risk of women developing pre-eclampsia.

#### Study setting {9}

The study will be conducted in up to 60 obstetric units in hospitals across the UK. A list of participating study sites can be found on the CaPE trial website: https://www.birmingham.ac.uk/research/bctu/trials/womens/cape/recruitment.

#### Eligibility criteria {10}

Various screening strategies to identify women at high risk of pre-eclampsia have been explored [20]. To date, NICE clinical risk factor screening, as listed below, remains the standard of care nationally for identification of high-risk women eligible for aspirin therapy in early pregnancy. A limited number of hospitals in the UK use the Fetal Medicine Foundation (FMF) algorithm to screen for risk of pre-eclampsia for aspirin eligibility [21]. In addition to the maternal risk factors included in NICE guidelines, the algorithm uses biophysical (mean arterial pressure, uterine artery doppler) and biochemical (placental growth factor, PAPP-A) markers; this algorithm has been found to have a better detection rate for pre-eclampsia and preterm pre-eclampsia compared to the NICE criteria for a 10% screen-positive rate [22]. However, as pre-eclampsia screening is an evolving area of research and national recommendations may change during the course of the trial, as a pragmatic approach, we will include women deemed to be eligible for aspirin based on NICE, FMF, or any other nationally accepted risk assessment tool. This will ensure findings will remain generalisable and clinically relevant.

There may be some women who are deemed eligible for aspirin but cannot take it due to contraindications. These women are still eligible to take part in CaPE and are particularly important to assess for calcium benefits.

##### Inclusion criteria

16 years of age or olderAble to provide informed consent.Confirmed viable pregnancy on a dating scan (usually done between 10 and 14 weeks) and any subsequent scansGestation 22^+0^ weeks or lessWomen deemed eligible for aspirin therapy based on the following:NICE guideline criteria as follows:Either at least one high-risk factorHypertensive disease during a previous pregnancyChronic renal diseaseAutoimmune disease such as systemic lupus erythematosus (SLE) or antiphospholipid syndromeType 1 or 2 diabetesChronic hypertensionor two or more moderate-risk factorsNulliparityAge 40 years or olderBMI 35 kg/m^2^ or more at first visitFamily history of pre-eclampsiaMultifetal pregnancyPregnancy interval of more than 10 yearsORThe Fetal Medicine Foundation (FMF) algorithm for pre-eclampsia risk assessment [21] ORAny other national pre-eclampsia screening criteria guidelines that may be used in the future

##### Exclusion criteria

Any known contraindications to regular calcium intake (history of renal stones, known renal impairment with pre-pregnancy eGFR < 30 mL/min/1.73 m^2^ or serum creatinine > 150 μmol/L, known history of hypercalcaemia or hypercalcaemia-causing diseases (e.g. parathyroid disease, sarcoidosis, malignancy)) and current severe persistent vomiting leading to dehydration or requiring hospitalisation*.*If persistent vomiting resolves, the woman may be reassessed for inclusion in the trial, providing all other inclusion and exclusion criteria are met.Use of drugs with potential for severe interactions with calcium: Digoxin or other cardiac glycosides, antiretroviral drugs for HIV treatment, antineoplastic drugs, and diuretics (thiazide, thiazide-like, or xipamide)—the latter two are not usually used in pregnancy [23]Use of any additional calcium supplement either on its own or as part of other multivitamin or vitamin D preparations and unable or unwilling to stop them or change to other multivitamins without calcium, as this could lead to higher doses of calcium supplementation in the calcium group and contamination in the placebo groupWomen who are taking vitamin D regularly in high doses > 1000 IU/day as supplements or for conditions such as malabsorption syndromes. Note: A short course of high-dose vitamin D (e.g. 20,000 IU weekly for 6 weeks) to treat vitamin D deficiency during pregnancy is not an exclusion criterionKnown contraindications to excipient isomalt (e.g. hereditary fructose intolerance)A diagnosis of pre-eclampsia in the current pregnancy, prior to trial entry

#### Who will take informed consent? {26a}

Women who are eligible will be approached by a member of the direct care team, which may include the maternity research team. Information about the trial will be provided both verbally and in writing via the participant information sheet (PIS). Women will be given time to consider participation in the trial and ask any questions they may have. If the women would like to take part in the trial, then a doctor trained in study procedures will confirm eligibility, and an appropriately trained (including good clinical practice (GCP) trained) individual will be able to take consent, providing that local practice allows this and responsibility has been delegated by the site principal investigator (PI). The participant’s study participation will be documented in the paper or electronic maternity records.

## Additional consent provisions for collection and use of participant data and biological specimens {26b}

The consent form states that participants will allow direct access to the medical records of the mother and baby if they agree to take part in the trial. Optional consent is available to take part in future research related to the study via electronic data linkage of routinely collected data from NHS databases and general practitioner records.

Consent for biological specimens is not applicable as no samples are being collected.

### Interventions

#### Explanation for the choice of comparators {6b}

The current standard of practice is not to give calcium supplementation; hence, no treatment aside from usual care is our comparator. We will use placebo tablets that contain no active ingredient and are manufactured to match the chewable tablets that are given to the intervention arm. The rationale for using a placebo is described in the section ‘Who will be blinded {17a}’. Participants are instructed to take one tablet in the morning and one in the evening.

### Intervention description {11a}

Participants randomised to the intervention arm will receive 2 g/day of calcium supplementation through oral, chewable tablets containing the equivalent of 1 g of calcium carbonate in each tablet. Participants will be instructed to take one tablet in the morning and one in the evening.

However, if the participant in the intervention or comparator arm is unable to take tablets in divided doses, they will be given the option to take both tablets at a more convenient frequency (i.e. at the same time) to improve adherence but will be advised of potential increase in risk of gastrointestinal side effects.

The dose of 2 g/day has been selected for this study to ensure the highest likelihood of detecting a difference in the risk of pre-eclampsia if one exists by using a high dose of calcium, without there being any known risks for women and their babies, based on the best available evidence from previous studies. Previous trials suggest a dose-dependent effect: a dose of 2 g/day is the highest, and most used dose among previous RCTs that show a significant reduction in the risk of pre-eclampsia [17]. One RCT directly comparing high-dose calcium (2 g/day) with low dose (500 mg/day) found a greater reduction in the risk of pre-eclampsia with 2 g/day [24], although a non-inferiority trial comparing 1.5 g/day with 500 mg/day did not find a significant difference [25]. The dose of 2 g/day administered in this trial is within the maximum daily intake unlikely to cause adverse health effects (tolerable upper intake level), which is around 2.5 to 3 g/day (for 19–50 and 14–18 years, respectively) during pregnancy [26]. A previous large randomised trial using a dose of 2 g/day in pregnant women with adequate baseline calcium intake (> 1 g/day) showed that it was not associated with any increase in adverse effects [27]. Thus, we aim to optimise efficacy without compromising safety, based on the best available evidence, and ensure the greatest likelihood of a definitive result for the trial.

The optimum time of starting calcium is unclear as the mechanism of action is not clearly understood. Over 90% of women in previous calcium supplementation trials were randomised at or prior to 22 weeks [17]. In line with previous trials, CaPE IMP may be started anytime from between 12 and 22 weeks. This will avoid IMP exposure in the first trimester, which is a time of greater teratogenic risk and randomisation at a time of greater pregnancy loss. Starting in the second trimester will also improve adherence as nausea and vomiting subside with advancing gestation. It is still early enough to potentially benefit women who are at risk of developing early onset pre-eclampsia. This timing will also coincide with routine antenatal appointments (dating and anomaly scan), making it easier and more efficient for clinicians to recruit and less time-consuming and inconvenient for women.

### Criteria for discontinuing or modifying allocated interventions {11b}

Discontinuation of the investigational medicinal product (IMP) may occur at either the request of the participant or clinician. The time and reason for discontinuation of the IMP will be documented, but unless the participant also expresses a desire to withdraw, they will remain in the trial and their outcome data collected. Similarly, if a clinical decision is made to discontinue a participant’s IMP usage, this will be documented, but in and of itself is not a reason to withdraw the participant.

Participants can withdraw from the trial at any time without giving a reason, and this will not impact their own (or their baby’s) ongoing care and standard clinic visits.

### Strategies to improve adherence to interventions {11c}

Adherence to the IMP will be captured through two methods: (1) A pill count where unused IMP is returned to the hospital at the end of pregnancy and (2) text messages to the participant enquiring about adherence to the IMP sent on a four-weekly basis. A ‘maintaining contact’ text message is also sent out monthly (2 weeks after the adherence text messages) to thank the participant for their time in the trial and to remind them to take their tablets as advised by their local care team. As a pragmatic trial, the regularity of these text messages is aimed at mimicking the frequency with which routine care contact may occur with the participant, both via clinic appointments and general healthcare phone calls and text messages which now form part of routine practice.

### Relevant concomitant care permitted or prohibited during the trial {11d}

Women commonly use other supplements or medications during their pregnancy that may impact or be impacted by calcium [23]. The common ones include the following:Iron: Calcium can decrease iron absorption. Women will be advised to take the trial tablets more than 2 h before or after any iron tablets. Vitamin D: Vitamin D impacts calcium absorption, and regular high doses may result in too much calcium in the blood (hypercalcaemia). For the CaPE trial, women can take part if they are on vitamin D supplements in a preventative dose (≤ 1000 IU) or short-term treatment dose of vitamin D (e.g. 20,000 IU weekly for 6 weeks) as it would be inappropriate to withhold these. Women will be asked not to use vitamin D supplements containing additional calcium. The use of or intention to use vitamin D will be recorded at the start of the pregnancy to confirm eligibility.Multivitamins: During pregnancy, women may routinely take multivitamins; however, whilst in the CaPE trial, they should not take multivitamins containing calcium, as this may lead to hypercalcaemia in the intervention arm or contamination of the placebo arm. Antacids: women will be advised to take non-calcium-based antacids, such as aluminium or magnesium-based antacid, to reduce the risk of hypercalcaemia. Proton-pump inhibitors (such as omeprazole) can also be used as alternatives.Thyroxine and hydroxychloroquine: Calcium may reduce their absorption, so women will be advised to leave a period of at least 4 h before taking their trial tablet if they use these medications.Folic acid: No known interaction with calcium, so women may take this as normal.

Women will be given a drug information sheet at the time of recruitment, which details what supplements and medications are suitable to take at what time point relative to the IMP. Otherwise, participants can receive concomitant care as clinically required.

Co-enrolment in other randomised controlled trials may be acceptable but must be discussed and agreed upon by the chief investigator (CI) and Trial Management Group (TMG).

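### The spacing advice for thyroxine and hydroxychloroquine covers only the time before a trial tablet, so taking these drugs soon after a tablet is not excluded

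*Protocol article*

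**What the plan says.** All the spacing rules are in the protocol article, in the section on relevant concomitant care {11d}. It opens by noting that "Women commonly use other supplements or medications during their pregnancy that may impact or be impacted by calcium" and then lists the common ones.

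- **Thyroxine and hydroxychloroquine**, where the advice reads: "Calcium may reduce their absorption, so women will be advised to leave a period of at least 4 h before taking their trial tablet". No interval is given for taking either drug after a tablet.
- **Iron**, also because calcium lowers its absorption: "Women will be advised to take the trial tablets more than 2 h before or after any iron tablets".

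The section adds that women receive a drug information sheet, "which details what supplements and medications are suitable to take at what time point relative to the IMP". The sheet itself is not reproduced.

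Two other places bear on the point. The exclusion criteria bar "Use of drugs with potential for severe interactions with calcium: Digoxin or other cardiac glycosides, antiretroviral drugs for HIV treatment, antineoplastic drugs, and diuretics" of specified types, and name neither thyroxine nor hydroxychloroquine. The intervention description {11a} sets the schedule: "Participants will be instructed to take one tablet in the morning and one in the evening". Women who cannot manage divided doses may take both tablets together.

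**The concern.** The rule is narrower than its own reason. If calcium lowers the absorption of these drugs, the two must be kept apart whichever is taken first. The sentence protects the order drug, then tablet, and is silent on tablet, then drug. The iron item spells out both directions, so a reader has some cause to take the different wording literally.

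What is at stake is the reliability of a co-medication instruction. Users of these two drugs are not excluded, and spacing is the only drug-specific precaution the article states for them. The placebo contains no active ingredient, so any interaction can arise only in women allocated calcium. Because the trial is blinded, the advice has to be right for everyone. No consequence for the treatment comparison is claimed.

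**Working it through.** There is no stated figure to reproduce. The check compares the two rules and then tests the one-way rule against the dosing schedule.

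**The rules side by side (section {11d})**

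| Item | Reason given | Gap before the tablet | Gap after the tablet |
|---|---|---|---|
| Iron | calcium lowers its absorption | more than 2 h | more than 2 h |
| Thyroxine, hydroxychloroquine | calcium may lower their absorption | at least 4 h | none stated |

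No other section of the article gives an interval for these two drugs.

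**Does the wording admit a dose soon after a tablet?** The article says only morning and evening, so assume tablets at 07:00 and 19:00.

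- Drug at 07:05: the next tablet is 11 h 55 min later. This is more than 4 h, so it complies, although calcium was taken 5 minutes earlier.
- Both tablets together at 07:00, drug at 07:05: the next tablets are 23 h 55 min later. This also complies.

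**What would a two-way rule cost in dosing time?** Inputs: two tablets a day; 4 h gap before each (stated); gap *g* after each (assumed). If the blocked periods do not overlap,

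permitted time = 24 − 2 × (4 + *g*) hours.

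With both tablets taken together there is one blocked period, so permitted time = 24 − (4 + *g*) hours.

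| Gap after the tablet | Tablets 12 h apart | Windows with tablets at 07:00 and 19:00 | Both tablets together |
|---|---|---|---|
| *g* = 0 (as written) | 24 − 8 = 16 h | 07:00–15:00, 19:00–03:00 | 24 − 4 = 20 h |
| *g* = 2 h (iron rule's figure) | 24 − 12 = 12 h | 09:00–15:00, 21:00–03:00 | 24 − 6 = 18 h |
| *g* = 4 h (symmetry) | 24 − 16 = 8 h | 11:00–15:00, 23:00–03:00 | 24 − 8 = 16 h |

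The twice-daily totals hold for any two tablets at least 8 h apart on both sides. These hours measure the burden of the correction, not exposure or harm. The article gives neither the number of users nor their intake times.

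**The case against.** The strongest reply is that the article is a summary and hands dose timing to the drug information sheet. The sheet may already be two-way, in which case women are properly advised. That stands as a limit: the defect is shown in the protocol wording, not in what women are told. It does not remove the point, because the article does not leave the matter open for the sheet to fill. It states a rule, and the rule runs one way. If the sheet differs, the two documents should be aligned.

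A second reply is that the sentence can be read as prescribing an order: drug first, a wait, then the tablet. With two tablets a day that does not close the gap. A dose at 20:00 precedes the 07:00 tablet by 11 h and so follows the order, yet it comes 1 h after the 19:00 tablet.

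Third, usual clinical care continues and clinicians can stop the trial tablets, so spacing is not the only protection. That is fair for general provisions; none is specific to these drugs. The exclusion criterion also concerns severe interactions, and nothing in the article places these two drugs in that class. Their absence from it is therefore not itself an error.

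Finally, the 4 h gap after the tablet appears nowhere in the article, and it leaves narrow windows on the twice-daily schedule. That is correct, which is why the interval in the fix is conditional on the sheet.

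**Conclusion.** The concern holds as a minor point. The advice covers one of the two orders in which drug and tablet can be taken, against its own reason and unlike the iron rule in the same list. As written, the gap is at least 4 h before a tablet and zero after it.

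The conclusion rests on the plain wording of the article. The drug information sheet could show that practice is already sound. Neither exposure nor harm can be quantified, and nothing here touches the primary outcome, power or analysis.

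**What to change.** Reword the item along these lines: *take the trial tablets at least 4 h before or after thyroxine or hydroxychloroquine*. Then check that the drug information sheet and site training say the same, and correct them if they do not. If the sheet already sets a different interval after the tablet, put that interval in the protocol instead of the assumed 4 h.

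The editorial cost is one phrase and one document check. The practical cost is tighter timing for the women concerned, as tabulated above. Where the remaining windows are awkward, the article already allows both tablets to be taken at once, with a warning about gastrointestinal side effects. Under the 4 h two-way rule that leaves 16 h a day.
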